Existing studies, however, involved predominantly chronic stroke patients. In our recent meta-analysis of predominantly chronic stroke cohorts, BCI rehabilitation produced a mean improvement of 5.23 points on the Fugl–Meyer Assessment Upper Extremity (95% confidence interval 3.85 to 6.61; total score range 0 to 66, with higher scores indicating less impairment), exceeding the established minimal clinically important difference of 4 to 6 points for the FMA-UE [24]. We hypothesize that there may potentially be greater benefits when BCI is applied during the acute/subacute phase when neuroplasticity is heightened. Notably, an overview of systematic reviews by Liu et al. (2025) concluded that BCI-combined treatment improves upper limb motor function and quality of daily life, with effects particularly pronounced in the subacute phase [25]. In acute and subacute stroke, several studies have alluded to moderate quality evidence and high safety profile and efficacy of BCI when coupled with end effectors such as FES, VR, or robots, achieving mean FMA-UE difference of 3.69–5.02 albeit with less robust gains for ADL independence. Subgroup analyses indicated that interventions < 30 days of stroke for <3 weeks may yield greater benefits, in particular paired with FES. Optimal training parameters suggested daily sessions of 20–90 min or 2–5 times weekly for 3–4 weeks [26,27] (Figure 1).

However, practical implementation of BCI technology within acute inpatient hospital settings presents logistical challenges and must also be carefully evaluated. The setup of EEG headsets with wet electrodes requires trained personnel and can add at least 10–15 min of preparation time per session, including set-down and scalp cleansing after MI-BCI to achieve adequate electrode impedance [28,29].

Lastly, economic data remain scarce, creating barriers to widespread implementation in healthcare systems [30]. Understanding the incremental cost-effectiveness of BCI rehabilitation compared to standard care is essential for informing policy decisions regarding technology adoption and reimbursement. This study therefore incorporates a prospective economic evaluation alongside the clinical feasibility assessment to generate preliminary cost-effectiveness evidence.

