### 2.3. Eligibility Criteria

**Inclusion criteria are as follows:** adults aged 21–80 years with confirmed hemorrhagic or ischemic stroke on neuroimaging, stroke onset within 2–12 weeks; demonstrated voluntary finger flexion or extension by Oxford Medical Research Council (MRC) grade 0–4/5, Montreal Cognitive Assessment (MoCA) score > 20/30; ability to understand written and spoken instructions; and stable medical and neurological status as determined by the clinical team [34]. Because the closed-loop paradigm depends on integrating afferent (proprioceptive and visual) feedback with efferent motor intent, lesion location will be documented from neuroimaging; participants with predominantly cerebellar or brainstem lesions—who may retain intact primary sensation yet have impaired updating of internal sensorimotor (forward) models, that is, impaired predictive coding—will remain eligible but will be flagged a priori. For such participants the intervention explicitly leverages the multimodal, error-corrective feedback intrinsic to the recoveriX loop (synchronized FES-evoked movement together with visual avatar feedback) as an externally supplied source of sensory prediction; their decoding performance and clinical response will be examined as an exploratory subgroup to determine whether impaired predictive coding attenuates BCI benefit and should inform eligibility for a future definitive trial. Because the motor-imagery-related event-related desynchronization (ERD) used for BCI classification is recorded over central sensorimotor electrodes (FC3–CP4) rather than posterior/occipital sites, cerebellar lesions are not expected to directly impair this signal; ERD magnitude and BCI performance in this subgroup will nonetheless be examined exploratively as above.

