A priori electrophysiological biomarkers of motor recovery, and their association with clinical change, will be defined and tested in a pre-specified manner. The primary candidate biomarkers are (i) the magnitude of event-related desynchronization and synchronization (ERD/ERS) in the contralesional and ipsilesional mu (8–13 Hz) and beta (13–30 Hz) bands during motor imagery; (ii) the hemispheric laterality index of sensorimotor ERD; (iii) the CSP-LDA classification accuracy and its session-to-session trajectory; and (iv) the recoveriX BCI compatibility index. The principal clinical anchor will be the change in FMA-UE from baseline to week 3–4, with change in ARAT as a secondary anchor. For each biomarker, both the baseline value and the within-training slope will be related to clinical change using Spearman rank correlation coefficients and, where the sample permits, robust linear regression adjusting for baseline motor severity, with 95% confidence intervals reported throughout. Given the exploratory sample size, these biomarker–outcome associations are explicitly hypothesis-generating; they will be interpreted descriptively, with Benjamini–Hochberg control of the false discovery rate, rather than as confirmatory tests, and will be used to nominate candidate predictive biomarkers for a future definitive trial.

As an exploratory predictor of treatment response and following reviewer suggestion, sensorimotor ERD will additionally be recorded during a brief action-observation task at baseline, in which the participant watches a filmed version of the to-be-performed hand movement. Motor imagery and action observation engage a largely shared frontoparietal network—the putative human mirror mechanism [43]—and a robust ERD elicited while observing a to-be-performed action has been associated with a favorable response to motor rehabilitation after stroke [44,45]. Baseline action-observation ERD will therefore be examined as a candidate stratifying biomarker and, potentially, as an eligibility-refining criterion for a future definitive trial rather than as a mandatory enrolment criterion in the present feasibility study.

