### 3.12. Data Analysis

Data analysis will be performed using Python (version 3.11; Python Software Foundation, Wilmington, DE, USA) programming language with established statistical packages. Descriptive statistics will be expressed as mean and standard deviation (SD) for normally distributed continuous variables or median with interquartile range (IQR) for non-normally distributed data. Given the small sample size characteristic of feasibility studies, non-parametric tests, including the Wilcoxon signed-rank test, will be employed for within-subject comparisons across time points. *p*-values will be corrected for multiple comparisons using the Benjamini–Hochberg False Discovery Rate (FDR) correction, with statistical significance set at alpha = 0.05 [51].

Pre-specified stratified and subgroup analyses will be undertaken. Given potentially divergent recovery trajectories between ischemic and hemorrhagic stroke, feasibility metrics and clinical outcomes will be reported separately for the ischemic and hemorrhagic subgroups, and where cell sizes permit, differences will be explored using exploratory between-subgroup comparisons (Mann–Whitney U tests for continuous outcomes and Fisher’s exact tests for proportions). Outcomes will likewise be summarized by baseline FMA-UE severity stratum (severe, 0–19; moderate-to-mild, 20–47) and, descriptively, by lesion location (cortical, subcortical, brainstem, or cerebellar). Because the feasibility sample (*n* = 12) is not powered for subgroup inference, all stratified analyses are explicitly exploratory and hypothesis-generating; they are intended to estimate the direction and variability of effects by stroke etiology and severity, will be reported with effect estimates and confidence intervals rather than an emphasis on *p*-values, and will inform pre-registered subgroup hypotheses for the future definitive trial.

Based on preliminary data from our meta-analysis of BCI rehabilitation in chronic stroke [24], we expect to observe improvements in FMA-UE scores with a mean change of approximately 5.23 points (standard error 0.70) by the end of 15 training sessions. Historical data from TTSH indicate a mean FMA-UE improvement from 29.1 to 37.4 points (+8.3 points) with standard rehabilitation [40]; thus, BCI may yield an expected total improvement of approximately 13–14 points if effects are additive.

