We highlight the following limitations: Without a concurrent control group, any observed changes cannot be definitively attributed to the BCI intervention versus spontaneous recovery in the acute/subacute phase. This is a particularly important consideration in the 2–12-week window, when substantial spontaneous neurological recovery occurs and follows broadly predictable, proportional-recovery-type trajectories, making the separation of intervention-related gain from natural recovery intrinsically difficult in a single-arm design. To characterize and bound this confounder, we will (i) benchmark the observed FMA-UE and ARAT trajectories against the spontaneous-recovery estimates derived from the propensity-matched historical controls and from published early-recovery models, (ii) examine whether within-training electrophysiological change (ERD/ERS and decoding accuracy) tracks clinical change more closely than the passage of time alone would predict, and (iii) present sensitivity analyses that attribute conservative proportions of the observed gain to spontaneous recovery. These steps cannot substitute for a concurrent randomized control arm, which remains the definitive solution and is planned for the subsequent trial. The use of historical controls for economic evaluation introduces potential residual confounding. However, this study is intended as a pragmatic feasibility study that would in future support a larger study. The small sample size (*n* = 12) is appropriate for feasibility but limits precision, subgroup analysis, and generalizability, meaning that all findings are intended as hypothesis-generating to inform a future adequately powered trial. A specific consideration in this early phase is patient selection: motor imagery is attention-dependent, and the fatigue, reduced concentration, and medical instability that are common soon after stroke may limit who can engage with the paradigm. Determining which acute and early subacute patients can tolerate and reliably operate the BCI is therefore an explicit feasibility output of this study and will be used to refine eligibility criteria for a future definitive trial.

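### The biomarker analysis adjusts for baseline severity but not for time since stroke, so a marker that only tracks time since stroke could be nominated for the definitive trial

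*Protocol article*

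**What the plan says.** Section 2.3 admits patients with "stroke onset within 2–12 weeks". Section 3.1 fixes the biomarker analysis. The clinical outcome is FMA-UE change over the 3–4 weeks of training, with ARAT change second. Each biomarker enters twice, as its starting value and as its slope over training, and is first correlated with that outcome by Spearman's method without covariates. The adjusted analysis is given as: "where the sample permits, robust linear regression adjusting for baseline motor severity, with 95% confidence intervals reported throughout". No other covariate is named. The associations are labelled hypothesis-generating, are to be read descriptively with Benjamini–Hochberg control, and "will be used to nominate candidate predictive biomarkers for a future definitive trial". The same section adds a baseline action-observation ERD measure that might later refine eligibility.

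Section 3.12 reports outcomes by stroke type and adds: "Outcomes will likewise be summarized by baseline FMA-UE severity stratum", with lesion location as a further descriptive split. Time since stroke is not on that list.

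Elsewhere the protocol does treat it as important. Section 3.3 makes time post-stroke at rehabilitation admission one of the four core matching variables for the historical controls. The Discussion says that in the 2–12-week window "substantial spontaneous neurological recovery occurs and follows broadly predictable, proportional-recovery-type trajectories". Its mitigation (ii) is to examine whether within-training EEG change follows clinical change more closely than elapsed time would predict.

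**The concern.** The anchor covers a fixed 3–4 weeks, but those weeks fall on different parts of the recovery curve. A patient enrolled at week 2 is measured over roughly weeks 2 to 6 after stroke; one enrolled at week 12, over roughly weeks 12 to 16. If spontaneous recovery slows across the window, as the Discussion's account suggests, FMA-UE gain will depend on entry time. Any biomarker that also varies with entry time will then correlate with gain even if it carries no other information about recovery. Neither the raw Spearman coefficient nor adjustment for baseline severity is designed to remove this.

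At stake is the stated use of the output. A marker that merely stands in for days since stroke could be carried into the definitive trial as a predictor of response, although the onset date would give the same information at no cost.

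**Working it through.** **Is the term absent?** Four places, side by side:
- Section 3.1, correlations: no covariates.
- Section 3.1, regression: baseline motor severity only.
- Section 3.12, strata: stroke type, FMA-UE severity, lesion location.
- Discussion, mitigation (ii): concerns change during training, names no model and no onset-to-baseline variable. It therefore does not cover baseline biomarker values, which are half of the planned predictors, or baseline action-observation ERD. Training lasts 3–4 weeks for everyone, so elapsed training time hardly differs between patients; time since stroke does.

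The plan states no figure on this point, so there is none to reproduce.

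**How large could the effect be?** Inputs from the documents: n = 12 (10 after the allowed dropout), entry between 2 and 12 weeks, alpha 0.05. Assumptions, not in the documents: entry time uniform over the window; biomarker and FMA-UE gain each have correlation of size r with time since stroke, in the same direction; no other link between them; severity independent of time.

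Under these assumptions the induced linear correlation is r × r: 0.3² = 0.09, 0.5² = 0.25, 0.7² = 0.49. Simulation gives the matching mean Spearman coefficient and the share of trials with p < 0.05 (4,000 trials per setting; least squares stands in for robust regression):

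| n | r | mean Spearman | Spearman | adjusted for severity | adjusted for severity and time |
|---|---|---|---|---|---|
| 12 | 0 | 0.00 | 5.0% | 4.9% | 4.6% |
| 12 | 0.3 | 0.08 | 5.7% | 6.2% | 5.2% |
| 12 | 0.5 | 0.23 | 11.2% | 11.4% | 5.1% |
| 12 | 0.7 | 0.47 | 36.7% | 35.3% | 5.2% |
| 10 | 0.3 | 0.07 | 6.0% | 5.6% | 5.3% |
| 10 | 0.5 | 0.24 | 11.5% | 10.0% | 4.6% |
| 10 | 0.7 | 0.46 | 29.3% | 27.9% | 4.8% |

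The partial Spearman coefficient given time since stroke is (ρ_by − ρ_bt ρ_yt) / √[(1 − ρ_bt²)(1 − ρ_yt²)], where b is the biomarker, y the gain and t the time since stroke. It is tested on n − 3 = 9 degrees of freedom at n = 12. In a separate run of 20,000 trials per setting at n = 12, its mean was at most 0.05 and it rejected in 5.2% to 6.2% of trials for r from 0 to 0.7.

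**Does false-discovery control deal with it?** Assume 28 tests (7 biomarkers × baseline or slope × 2 anchors), n = 12 and every biomarker equally exposed. After Benjamini–Hochberg the share of tests falsely flagged is about 0.4% at r = 0.3, 1.5% at 0.5 and 17–18% at 0.7. The chance of at least one false flag is about 9%, 22% and 62–68%, against 6–7% at r = 0. The per-test rate falls, but the bias remains.

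**The case against.** The strongest reply has four parts.

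- **The analysis is exploratory.** It is to be read descriptively under false-discovery control, so a single nominal 5% test is not the planned decision rule. That stands and lowers the severity. It does not answer the point, because false-discovery control addresses multiplicity, not confounding, and the output has a stated use.
- **The confounder is already acknowledged.** The Discussion plans benchmarking against controls matched on time post-stroke, the comparison with passage of time, and sensitivity analyses for spontaneous recovery. That is partial cover. Benchmarking and the sensitivity analyses concern average gain, not which patients within the cohort gain more. The model behind (ii) could sit in an unseen analysis plan, but Section 3.1 already names the adjustment set and leaves time out.
- **The premise on EEG is undocumented.** Nothing in the protocol says that ERD or accuracy slopes are larger early. Section 3.1 notes fluctuating vigilance early after stroke, so the direction for decoding accuracy is open. This stands; the correlations above are assumptions, and weak ones do negligible harm.
- **Adjustment can remove signal.** If timing acts on recovery partly through these EEG measures, conditioning on time takes away some of what the trial seeks. This stands and argues for reporting both coefficients rather than replacing one.

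A reader might also infer that the trial leaves its own hypothesis of earlier benefit untested. The documents do not support that. The Background hypothesises more benefit in the acute or subacute phase than in chronic stroke, not a gradient within weeks 2 to 12. The remark that "interventions < 30 days of stroke for <3 weeks may yield greater benefits" reports other studies' subgroup analyses, and Section 2.5 lists no timing hypothesis.

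**Conclusion.** The point holds in a limited form. The biomarker models omit a variable that the protocol itself treats as a confounder, and the one stated mitigation neither specifies it nor reaches the baseline values. A marker that only tracks time since stroke could therefore be nominated.

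How likely this is cannot be derived from the documents. On the assumptions given, it is negligible when both correlations with time are about 0.3 and material from about 0.5. If severity is itself related to time since stroke, the planned severity adjustment would remove part of the effect. It would be too strong to say that the planned correlations will be spurious; the documents support only that they could be, and that the plan as written could not tell. No primary feasibility endpoint is touched. Severity is low to moderate.

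**What to change.** In Section 3.1:
- Keep the raw Spearman coefficient and report beside it the partial Spearman coefficient given days from stroke onset to baseline, each with its 95% confidence interval.
- Add that variable to the robust regression where the sample permits; otherwise give the model with it as a sensitivity analysis.
- Show the correlation of days since stroke with FMA-UE change as a benchmark for the biomarkers.
- State that a biomarker's association is to be read together with its time-adjusted estimate before the biomarker is nominated for the definitive trial.

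In Section 3.12, add a descriptive plot of FMA-UE change against time since stroke. With 10 to 12 patients, subgroup tests by time would add little and are not needed.

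The cost is wording, one degree of freedom and slightly wider intervals. No new data are required, since time from onset is already needed to establish eligibility.

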### 3.2. Economic Evaluation

An incremental cost–utility analysis (CUA) will be conducted alongside the feasibility study to generate exploratory cost data of BCI rehabilitation compared to standard care, acknowledging the limited precision afforded by the single-arm design. The economic evaluation will adopt a healthcare system perspective over a 24-week time horizon, consistent with the clinical follow-up period.

To keep the economic evaluation focused, it is organized around two scopes: (1) the within-trial 24-week cost–utility analysis from a healthcare-system perspective described above and (2) a secondary long-term extrapolation. For the latter, a cohort state-transition (Markov) model, structured around post-stroke functional health states (for example, FMA-UE severity together with functional dependency) and an absorbing death state, will project costs and quality-adjusted life years over 2-year and 5-year horizons, using an annual cycle with half-cycle correction and discounting at 3% per annum (0% and 5% in sensitivity analysis), consistent with Singapore health-technology-assessment norms. Transition probabilities and utilities will be derived from the trial, the TTSH registry, and the published literature; a societal perspective incorporating productivity losses and informal caregiver time will be explored as a sensitivity analysis rather than as a primary scope. As it remains uncertain whether clinical gains from BCI-rehabilitation are sustained into the chronic phase beyond the trial follow-up period, all estimates extrapolated beyond 24 weeks will be treated as exploratory and interpreted with caution. Structural and parameter uncertainty will be characterized through deterministic and probabilistic sensitivity analyses, reported in accordance with CHEERS 2022.

### 3.3. Comparator Group: Historical Controls

Given the single-arm feasibility design, the comparator group will be derived from the TTSH stroke rehabilitation registry (2017–2025). Historical controls will be propensity-matched to BCI participants based on (1) baseline FMA-UE score, (2) age, (3) stroke type (hemorrhagic vs. ischemic), and (4) time post-stroke at rehabilitation admission (2–12 weeks). To reduce residual confounding, the propensity model will additionally include sex, baseline functional status (admission FIM and MBI), comorbidity burden (Charlson Comorbidity Index), clinically relevant concomitant medications (for example antispasticity and mood-active agents), the total inpatient rehabilitation therapy dose, and the calendar year (era) of admission. Historical control data will be obtained from an institutional inpatient stroke rehabilitation cohort assembled between 2022 and 2025 (more than 100 patients), for which baseline and discharge EQ-5D-5L utilities and FMA-UE scores are available to support propensity matching and quality-adjusted life year estimation. Corresponding inpatient rehabilitation cost data will be obtained from hospital administrative and costing databases. FMA-UE categories may use severe impairment (FMA-UE 0–19) and moderate-to-mild impairment (FMA-UE 20–47). This approach has been previously validated in the TTSH setting for evaluating upper extremity recovery outcomes [40]. Matching will be performed using nearest-neighbor propensity score matching with a caliper of 0.2 standard deviations to ensure adequate balance on baseline covariates. The matching ratio will be 1:3 (BCI/control) to maximize statistical power while maintaining adequate matching quality. Balance diagnostics will be assessed using standardized mean differences (target < 0.1 for all covariates) and variance ratios. To limit temporal confounding arising from the eight-year registry window (2017–2025)—over which ward staffing, rehabilitation protocols, and case-mix may have changed—the primary comparator analysis will be restricted to the contemporaneous 2022–2025 inpatient cohort, calendar year will be included as a matching and adjustment covariate, and models will additionally be fitted with admission era as a fixed effect; the influence of the matching window will be examined in sensitivity analyses that progressively restrict controls to narrower, more recent time bands. Sensitivity analyses will explore alternative matching specifications, including different caliper widths and matching algorithms (genetic matching, coarsened exact matching) to assess robustness of findings to matching choices. If precise stroke onset dates are unavailable for historical controls, hospital arrival date will be used as a proxy, consistent with Singapore Stroke Registry methodology.

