### 2.4. Sample Size

Based on comparable feasibility studies in BCI stroke rehabilitation literature and recommendations from our recent meta-analysis [24], a sample of 10 subjects will be sufficient for this feasibility study. Accounting for a 20% dropout rate (*n* = 2), the final proposed sample size is 12 participants. Recruitment will aim to stratify the sample by stroke type in an approximate ratio of 40% hemorrhagic (ICH) to 60% ischemic (infarct) stroke, consistent with local case-mix.

This sample size follows established guidance for pilot and feasibility trials, in which the objective is to estimate feasibility parameters and their variability rather than to test efficacy; widely cited recommendations propose approximately 12 participants for pilot studies [35,36], and a sample of 10–12 is adequate to estimate a feasibility proportion of about 80% (for example recruitment or adherence) with a 95% confidence interval half-width of roughly ±20%. A formal efficacy-based power calculation is therefore not appropriate for the present feasibility endpoints. Nonetheless, to inform the design of a future definitive trial, an indicative a priori power calculation was performed in G*Power (version 3.1). Anchoring conservatively on 6 points—the lower end of the FMA-UE minimal clinically important difference range established largely in chronic stroke (4–6 points)—acute-stroke-specific estimates are reportedly higher, approximately 7–10 points, but 6 points was retained as a conservative estimate and the pooled effect implied by our meta-analysis (mean change 5.23 points, standard error 0.70; approximate standard deviation 3.4 in the analyzed cohorts) [24]; a two-sided paired within-group comparison (α = 0.05, power = 0.80) would require approximately 6–8 participants to detect a change of the minimal clinically important difference magnitude, whereas a two-arm parallel comparison designed to detect a 4-point between-group difference at an assumed standard deviation of 6 (Cohen’s d ≈ 0.67) would require approximately 37–46 participants per arm. The variance and recruitment-rate estimates generated by the present feasibility study will be used to refine these calculations and to power the subsequent randomized controlled trial.

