**Concomitant Therapy:** Following each recoveriX session (approximately 30 min), participants will receive 60 min of standard-of-care conventional occupational therapy within 30–60 min of BCI training completion, resulting in a total therapy time of 90 min per session. This represents additional therapy (approximately 30 min) compared to standard care [40]. We acknowledge that as designed, this adjunctive schedule confounds the specific effect of closed-loop BCI neurofeedback with the effect of additional therapy time so that any functional gain cannot be attributed unambiguously to the brain–computer interface rather than to a greater rehabilitation dose. An adjunctive design was nonetheless chosen for pragmatic and ethical reasons in this acute inpatient population, in which withholding standard therapy in order to time-equate the arms would be inappropriate and the primary aim is feasibility rather than efficacy. To mitigate this confounder, we will (i) prospectively record the total upper limb therapy dose (in minutes and repetitions) for both BCI participants and historical controls, (ii) enter total therapy time as a covariate in exploratory effectiveness and cost analyses, and (iii) report the incremental cost of the additional therapist time separately from device-related costs. For the future definitive trial, a dose-matched (time-equated) active comparator—delivering an equivalent duration of conventional or sham/attention-controlled therapy—is planned so that the independent contribution of the closed-loop BCI can be isolated. Standard inpatient multidisciplinary stroke rehabilitation therapies will continue throughout the inpatient rehabilitation period. To prevent potential contamination of therapeutic effects, standard non-invasive upper limb FES over the forearm finger extensor muscle groups will not be applied during the inpatient stay where possible.

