### 3.5. Cost Perspective and Therapy Time Differential

The BCI intervention is modeled as additional adjunctive therapy in addition to standard of care rather than a substitute for standard care. Under this assumption (Scenario A), BCI participants receive 30 min of BCI training plus 60 min of standard occupational therapy per session (90 min total), whereas standard care patients receive approximately 60 min of occupational therapy per session based on TTSH rehabilitation protocols [40]. The incremental cost of BCI therefore includes both equipment-related costs and the additional 30 min of therapist time per session. Where available, actual billed charges from hospital administrative databases will be used to estimate healthcare costs. For intervention-specific costs not captured in routine billing (e.g., BCI equipment depreciation, additional therapist time), unit costs will be derived from institutional costing data. This pragmatic approach balances data availability with accuracy of cost estimation. A sensitivity scenario modeling partial substitution—approximately 25%, rather than 50%, of within-session supervision withdrawn from the midpoint of the training course following an initial supervised orientation period, noting this proportion may vary in practice—will be examined to explore conditions under which a favorable ICER may be achievable.

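### Therapy dose, which the intervention itself raises, is matched on and adjusted for in the historical-control comparison, and calendar year may leave few or no controls to match

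*Protocol article*

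**What the plan says.** Section 3.3 names four core matching variables: baseline FMA-UE, age, stroke type and time since stroke. It then extends the propensity model with sex, admission FIM and MBI, the Charlson index, relevant medications, and "the total inpatient rehabilitation therapy dose, and the calendar year (era) of admission". The stated aim of the matching is balance on baseline covariates. The method is nearest-neighbour matching, 1:3, with a caliper of 0.2 SD, and balance is judged by "standardized mean differences (target < 0.1 for all covariates" together with variance ratios. The primary comparator is restricted to a 2022–2025 cohort of more than 100 patients. Calendar year is matched on and adjusted for, and further models carry admission era as a fixed effect.

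Section 2.6 (Concomitant Therapy) acknowledges that BCI comes with extra therapy time. As mitigation it will "prospectively record the total upper limb therapy dose (in minutes and repetitions) for both BCI participants and historical controls" and "enter total therapy time as a covariate in exploratory effectiveness and cost analyses".

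Section 3.5 treats the same time as part of what is being evaluated: "The incremental cost of BCI therefore includes both equipment-related costs and the additional 30 min of therapist time per session". Table 2 also lists total OT/PT sessions and length of stay among the inpatient costs of both groups.

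On numbers, section 2.4 states that "the final proposed sample size is 12 participants". Section 3.14 places trial registration, still to come, before enrolment, so recruitment had not begun when the article was written.

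**The concern.** A propensity model for the effect of adding BCI should contain variables fixed before treatment. Therapy dose is not one of them. It builds up during the stay, it is higher in the BCI group by design, and it is a component of the cost outcome. Conditioning on it asks what BCI would do if it brought no extra therapy time, whereas section 3.5 asks what it costs and achieves to add BCI to standard care. The plan does not separate these two questions.

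Calendar year raises a different difficulty. If BCI participants and controls come from different years, year identifies the group, and neither matching nor an era effect can separate it from treatment.

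At stake are the exploratory cost–utility result and, in part, the benchmarking of FMA-UE and ARAT recovery against matched controls described in the Discussion.

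**Working it through.** **The plan's own figures.** "a sample of 10 subjects will be sufficient for this feasibility study"; adding 20% gives 10 × 1.2 = 12, as stated. Session time is 30 + 60 = 90 minutes with BCI, against about 60 in standard care.

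**Built-in dose difference, if BCI minutes count.**
- 15 sessions: 15 × 90 = 1350 against 15 × 60 = 900 minutes, a difference of 450 (+50%).
- 12 sessions: 1080 against 720 minutes, a difference of 360.

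**Model size.** Core variables 4; sex, FIM, MBI and Charlson 4; medications 1 (2 if the two example classes are separate terms); dose and year 2. The total is 11 or 12 terms. Treated participants per term: 12/11 = 1.09 or 12/12 = 1.00.

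**Effect of dose on the matching.** The article gives no SD for dose, so the shift was varied in a simulation. It had 12 treated, 100 or 150 controls, nine other covariates with no true group difference, a logistic propensity score, greedy 1:3 matching and a caliper of 0.2 SD of the logit. With dose in the model and year left out:

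| Dose shift (SD) | Treated with at least one match, 100 controls | Same, 150 controls |
|---|---|---|
| 0.5 | 10.7 of 12 | 11.1 of 12 |
| 1.0 | 9.5 | 10.2 |
| 1.5 | 7.8 | 8.8 |
| 3.0 | 1.6 | 2.2 |

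The matched controls lay about 0.4 to 1.7 SD above the average control dose. Because OT/PT sessions and length of stay are cost items, such controls can be expected to be costlier than usual, which would understate the incremental cost.

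**Effect of dose as a covariate.** Assume, for illustration only, a direct effect of 0.5, a dose effect of 0.3 per SD and a shift of 1 SD. The total effect is 0.5 + 0.3 × 1 = 0.80. The simulated dose-adjusted estimate was 0.51. With an assumed unmeasured factor driving both dose and outcome it was 0.25, which is neither the total nor the direct effect.

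**Calendar year.** Enrolment dates are not stated, so three cases were run with dose and year both in the model, over both pool sizes:
- All enrolled after 2025: complete separation in every run; 0 of 12 matched at any dose shift.
- Enrolled across 2025–26, dose shift 0.5–1.5 SD: complete separation in 31–86% of runs; 2.2 to 5.6 of 12 matched.
- All enrolled in 2025, same shifts: complete separation in 1–39%; 6.6 to 11.6 of 12 matched.

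**Balance target.** With 12 against 36 and no true difference, the chance SD of one standardized mean difference is √(1/12 + 1/36) = 0.333. For a single covariate, P(|SMD| < 0.1) = P(|Z| < 0.3) = 0.24 without matching. In the matched simulations the target was met on all covariates in at most 0.5% of runs in the scenarios with a dose shift or non-overlapping years. With dose and year removed (nine covariates) it was met in 0–1%, and with the four core variables alone in 11–15%.

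**After removing dose and year.** With nine covariates, complete separation fell to 0% and about 11 of 12 had at least one match. All 12 had three controls in only 0–8% of runs.

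**The case against.** The strongest defence is that the comparison is secondary and labelled exploratory, that residual and dose confounding are acknowledged, and that adjusting for dose answers a legitimate question about the effect net of therapy time. That last part stands, provided the analysis is labelled as such and kept apart from the main comparison. The planned sensitivity analyses do not help here: they vary caliper, algorithm and time band, and none drops dose or year.

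Dose is also not defined in section 3.3. If BCI minutes were excluded, overlap would improve and the 450-minute shift would not apply. Dose would still be a post-baseline variable, and section 2.6 records total upper limb dose in both groups.

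A reader might infer more than the document supports:
- *That the matching cannot work at all.* The result of no matches requires all enrolment after 2025. The article gives no enrolment dates, calls the 2022–2025 cohort contemporaneous, and gives its size only as a minimum. With enrolment in 2025 many participants can be matched.
- *That the ICER formula strips out the extra therapist time.* Section 3.7 defines the ICER as a plain difference in means, and section 3.5 costs the extra time directly. Only the adjusted analyses of section 2.6 condition on dose directly; the ICER is affected through the choice of matched controls.
- *That multiplying 0.24 across the covariates gives the chance of meeting the balance target.* That treats the covariates as independent and the groups as unmatched. Matching reduces imbalance, and FMA-UE, FIM and MBI are plausibly correlated. The 0.1 figure is also called a target, not a condition for analysis.
- *That the model must be cut to four variables.* That is one option, not something the document's errors require. How the control pool is screened for eligibility is detail that an article may leave to the full protocol.

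Describing the recording of historical controls' dose as prospective is a slip of wording and carries no weight here.

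**Conclusion.** The point holds for therapy dose without any assumption about enrolment. A post-baseline component of the intervention is placed in a model meant for baseline balance and is used as an adjustment covariate, while the costing section counts it as part of the BCI increment. The size of the distortion depends on the spread of dose among controls and on whether BCI minutes count, neither of which is given.

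The point on calendar year is conditional: total loss of matches if enrolment falls after 2025, partial loss with partial overlap. The balance target is very unlikely to be met at 12 against 36 and stays hard to reach even after dose and year are removed.

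This should be fixed, but it does not threaten the trial. The primary feasibility outcomes do not use the matched set. The Discussion's recovery benchmark also draws on published early-recovery models, so it does not rest on the matched controls alone.

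**What to change.** - Section 3.3: remove total therapy dose from the propensity model.
- Section 2.6: remove total therapy time from the main cost and effectiveness comparison and report it descriptively in both groups. Label any dose-adjusted result as a separate exploratory analysis of the effect net of dose.
- Section 3.3: state that, where enrolment years do not overlap the control window, calendar year leaves the propensity model and the era fixed effect is dropped. Rely then on the 2022–2025 restriction and the narrower-window sensitivity analyses already planned.
- Section 3.3: report the achieved standardized mean differences and how many of the 12 participants were matched, and do not present a value below 0.1 on every covariate as expected.

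The cost is rewording of two sections, with no new data. The price is that dose and, where dropped, calendar year are no longer formally balanced. Both remain stated limitations, and for dose the article already plans a time-equated comparator in the future trial.
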